### Sample and recruitment

The sample size was calculated for 230 members of the Diabetes Association of La Rioja (ASDIR) aged 18 years or older and diagnosed with type 2 diabetes mellitus.

A 95% confidence level and a 5% margin of error were used, values commonly accepted in community intervention studies [22]. Additionally, a dropout rate of 15% was anticipated, in line with that observed in previous studies conducted with populations with type 2 diabetes in similar contexts, where dropout rates range between 10% and 20% during multi-month interventions [23–26]. This estimation takes into account factors such as advanced age, disease burden, and the potential for low adherence to behavioral change programs. With these parameters, the final adjusted sample size is 169 individuals. Through a sequential allocation process based on the order of informed consent signing, approximately half will be assigned to the control group (CG) and the other half to the intervention group (IG), resulting in 84 participants in the CG and 85 in the IG.

To make it known to the associated and to know their willingness to participate, the president of the association will proceed to send emails and a broadcast message on WhatsApp through the community group. The dissemination of the project will begin in April 2025 and will last a total period of two months. Those interested and who meet the inclusion criteria will be selected during the following month for the study. A face-to-face visit will be made to the Association to explain the detailed bases of the Project and to sign the informed consent, while the group allocation will be carried out simultaneously. The study will last for a total of 12 months from the date of informed consent signature. Fig 1 presents the flowchart outlining the planned process of sample selection, recruitment, and participant allocation for this study.

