Regarding the handling of missing data, a descriptive analysis will be conducted to identify its pattern and proportion. An intention-to-treat (ITT) analysis will be adopted, including all participants assigned regardless of their adherence or losses during follow-up. For quantitative variables with missing data, multiple imputation will be applied using the Multiple Imputation by Chained Equations (MICE) method, generating several complete datasets that will be analyzed to improve accuracy and reduce bias. Additionally, a sensitivity analysis will be performed comparing results from imputed and complete data to assess the robustness of the conclusions.

One of the objectives of the study is to evaluate how the reduction of sedentary time is related to improvements in clinical parameters such as glucose, lipid and blood pressure levels. To this end, Pearson correlations will be used to analyze the relationship between sedentary time (measured with accelerometers) and changes in these parameters. In addition, multiple linear regression models will be used to adjust the analyses for possible covariates (age, sex, antidiabetic treatment, etc.).

Subgroup analyses based on relevant participant characteristics (such as age, sex, and level of motivation to change) will be considered exploratory and conducted with the aim of identifying possible differences in response to the intervention. To control for multiplicity across primary and secondary outcomes, the Bonferroni correction will be applied to adjust the significance level and minimize false positives. Given the relatively small number of comparisons, this conservative approach is appropriate and unlikely to substantially reduce statistical power. Results from these analyses will be interpreted with caution.

Changes in quality of life and motivation to change will be analyzed using the corresponding validated questionnaires. Both will be analyzed using repeated measures analysis of variance or linear regression to determine whether the interventions have a positive impact on these aspects over time.

The reliability and validity of the instruments used, such as the SBQ and the ActiTrainer accelerometer, have been verified. These instruments will measure sedentary lifestyle in an objective and reliable manner. On the other hand, the internal validity of the MTCEJ and DQOL Questionnaire has also been evaluated by psychometric analysis.

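### Comparing MICE with complete-data results does not test departures from missing at random, so agreement between them is not evidence of robustness to outcome-related dropout

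*Protocol article*

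**What the plan says.** The Statistical analysis section of the protocol article plans a description of the pattern and proportion of missing data, an intention-to-treat analysis of everyone assigned, and MICE for quantitative variables. It then states that "a sensitivity analysis will be performed comparing results from imputed and complete data to assess the robustness of the conclusions". Both the comparison and its purpose are therefore fixed in the text.

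Under Sample and recruitment, "a dropout rate of 15% was anticipated", with support from earlier studies in which "dropout rates range between 10% and 20% during multi-month interventions". The estimate is said to reflect "factors such as advanced age, disease burden, and the potential for low adherence to behavioral change programs".

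Two further passages bear on the point. Participants in both groups are measured at T0, T1 (3 months), T2 (6 months) and T3 (12 months). The section on the level of sedentary lifestyle plans a separate sensitivity analysis, with no stated content, for accelerometer records that miss the valid-day criteria.

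**The concern.** MICE as described assumes that, given the observed data, those who leave resemble those who stay. Complete-data analysis makes its own assumption, which also rules out dropout driven by unseen outcomes. Comparing the two can say something about missing completely at random versus missing at random. It cannot say what happens if missing at random itself is wrong.

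One such departure is easy to picture in this trial. Only the intervention group has sessions, calls and a visit to disengage from, and the plan names "the potential for low adherence to behavioral change programs" as one reason for dropout. If people who disengage lose the benefit, both analyses err in the same direction. Similar results could then be reported as robust while the effect among all assigned participants is overstated, and that effect is the stated intention-to-treat target.

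**Working it through.** **1. The plan's dropout figure.** The plan gives 230 members and says that "A 95% confidence level and a 5% margin of error were used". With a proportion of 0.5 (assumed; not stated), the finite-population formula gives

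n = 230 × 1.96² × 0.25 / (0.05² × 229 + 1.96² × 0.25) = 220.892 / 1.5329 = 144.1.

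144 / 0.85 = 169.4, so the stated 169 reproduces and includes the 15%. The split is given as "resulting in 84 participants in the CG and 85 in the IG". Dropout in the intervention group is then 0.15 × 85, about 13 people.

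**2. Assumptions for scale (not in the document).** Completers gain 45 min/day (E) at every post-baseline visit. The SD is 90, the correlation is 0.6 (r) between any two visits, and intervention dropouts have no effect at any visit. Dropout is p = 0.15 in both arms, and imputation is by arm.

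**3. Expected results.**
- True all-assigned effect: (1 − p)E = 0.85 × 45 = 38.25.
- Complete cases: E = 45. Overstatement 45 / 38.25 − 1 = 17.6%. In general it is 1/(1 − p) − 1, that is 11% at 10% dropout and 25% at 20%.
- MICE: when a dropout has k post-baseline values, each observed visit has regression weight b = r / (1 + k r). Each value lies E away from the completers' mean, so the imputed T3 benefit is E(1 − k b). The estimate is (1 − p)E + pE(1 − k b).

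| Dropouts' observed visits | b | Imputed benefit | MICE estimate | Overstatement | Gap to complete cases |
|---|---|---|---|---|---|
| T0 only (k = 0) | – | 45.0 | 45.0 | 17.6% | 0 |
| T0, T1 (k = 1) | 0.375 | 28.1 | 42.5 | 11.0% | 2.5 |
| T0, T1, T2 (k = 2) | 0.273 | 20.5 | 41.3 | 8.0% | 3.7 |

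Simulation under the same assumptions agrees. With T2 as the last visit, truth was 38.3, complete cases 45.2 and imputation 41.5. With T0 only, they were 37.4, 43.7 and 43.8.

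**4. Would the gap be noticed?** Completers number 84 × 0.85 = 71.4 and 85 × 0.85 = 72.25. Baseline-adjusted SD is 90 × √(1 − 0.36) = 72. The standard error is 72 × √(1/71.4 + 1/72.25) = 12.0 min. A gap of 3.7 min is about 0.3 standard errors and would normally be read as agreement.

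**5. A different mechanism.** A second simulation used a true effect of 0.4 SD, 15% missing at T3 in both arms, and logistic dropout with slope 2. All three settings are assumptions.
- When intervention-group dropout depended on the unseen T3 value or the unseen change, complete cases exaggerated the benefit by 0.08 to 0.18 SD and imputation by 0.10 to 0.14 SD. The two lay within 0.1 SD of each other in 87 to 99% of runs.
- When dropout depended on T3 alike in both arms, neither was biased (0.008 SD or less).
- When it depended on T2 and T0 to T2 were observed, both were close to unbiased.

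**6. What a delta run would show.** If intervention dropouts do worse than predicted under missing at random by delta, the estimate moves by p × delta. For delta = 0.5 SD this is 0.15 × 0.5 = 0.075 SD, or 0.05 to 0.10 SD for 10 to 20% dropout. The planned comparison holds delta at zero throughout.

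**The case against.** The strongest reply is that MICE and complete-case analysis rest on different assumptions and that the design gives MICE something to work with. This stands. With T1 and T2 measured, non-responders who leave later inform their own imputations, and MICE removes more than half of the bias (41.3 against 45, with 38.25 true). A reader might infer that the two analyses agree by construction, or that MICE will be 18% too large. Under these assumptions that is so only when dropouts leave no informative post-baseline data.

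The sizes also follow from the assumption of zero benefit in intervention dropouts. For the same reason, control-based imputation recovers the true value in such a simulation because it shares that assumption, which does not prove it right for this trial.

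Nor does the document say that dropout depends on unseen outcomes. Low adherence is one of three factors offered for the 15%, and age and aspects of the disease are recorded and could enter the imputation model.

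A reader might also infer that this is the only sensitivity analysis touching missing data. The accelerometer analysis is another, but its content is not stated and it does not cover the questionnaire outcomes.

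Finally, further sensitivity analyses are often left to an analysis plan that is not shown here. Their absence alone would be no finding. The point rests on what the text does state: a comparison given a purpose that it cannot serve.

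**Conclusion.** The concern holds in a limited form. Agreement between MICE and complete-data results is not evidence of robustness to dropout linked to lost benefit in the intervention group. Under the stated assumptions at 15% dropout, complete cases overstate the all-assigned effect by about 18%. MICE overstates it by about 8% when T1 and T2 are observed without benefit, and by up to about 18% with baseline data only. With outcome-related dropout alike in both arms there may be no bias. The document does not establish that the result will be overstated, only that the planned check may not reveal it. This is an inexpensive improvement to the analysis and does not put the main method in doubt.

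**What to change.** Keep MICE as the main analysis and state that the imputation model includes the T0, T1 and T2 values. For the primary outcomes (SBQ and accelerometer sedentary time, and the motivation questionnaire), add at least one sensitivity analysis that departs from missing at random by arm:
- a delta-adjusted run that worsens the imputed values of intervention dropouts in steps until the conclusion changes (tipping point), with a judgement on whether that delta is plausible; and/or
- control-based imputation, in which intervention dropouts are imputed from the control-group model.

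The complete-data comparison can stay as a description. If no such run is added, word the robustness statement as holding under missing at random only.

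The cost is a few more runs of the same imputation, with no change to data collection or sample size. The sensitivity estimate will probably be somewhat less favourable than the main one.

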**Design and methodology:**

Quasi-experimental controlled study, single-center, parallel, two-branch, with a 12-month follow-up. We plan to recruit up to a total of 169 participants, who will be assigned in a 1:1 ratio to a control group (who will receive e-mails) and an intervention group (who will receive face-to-face group and individual visits and telephone calls). The active intervention has a duration of 6 months and will be carried out by nursing professionals. The primary outcomes are sedentary time measured with the Sedentary Behavior Questionnaire (SBQ) and the use of accelerometers, and the state of motivation to change measured through the Transtheoretical Model of Physical Exercise Change Questionnaire (TMPECQ).

**Trial registration.** ClinicalTrials.gov (NCT06893146).

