#### State of motivation to change.

Measured by the TMPEC questionnaire (S5 Appendix). This questionnaire aims to identify which stage of the transtheoretical model of change a person is in regarding his or her willingness to engage in physical exercise. The stages of change include precontemplation, contemplation, preparation, action, maintenance, and relapse. The questionnaire has items that use a respond scale from 1 (strongly disagree) to 5 (strongly agree) of reasons for not exercising, these items should only be completed by participants who do not exercise regularly. Similar items are rated in the table with the reasons why the participants perform physical exercise on a regular basis, the answers are rated on the same Likert-type scale from 1 to 5. The measurement of the questionnaire is performed by analyzing the average score of each corresponding stage of the transtheoretical model of change. Higher scores on each subscale of the questionnaire reflect a greater identification with the corresponding stage of behavioral change. Specifically, mean scores equal to or greater than 4 indicate a strong identification with that stage. A significant change can be interpreted as an increase of 0.5 points or more in the mean score of a subscale. Thus, increases in the mean scores of the preparation, action, and maintenance stages are considered indicative of progress in motivation toward the adoption and consolidation of regular physical exercise. Conversely, high scores on the precontemplation subscales reflect low readiness for change or resistance to modifying sedentary behavior. The internal consistency of this questionnaire shows Cronbach’s Alpha values>0.70 for each of the factors resulting from the factor analysis: precontemplation (0.71), contemplation (0.71), preparation (0.75), action (0.71) and maintenance (0.70) [43].

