### Statistical analysis

First, a descriptive analysis of the sociodemographic, clinical and anthropometric data of the participants will be performed. Quantitative variables (such as age, BMI, glucose, cholesterol and blood pressure levels) will be described using means ± standard deviation (for those with normal distribution) and medians (with 25^th^ and 75^th^ percentiles) when they do not follow a normal distribution. Qualitative variables (such as sex, educational level, and marital status) will be described as relative frequencies, cumulative relative frequencies, and percentages. These analyses will be performed using Microsoft Excel for data organization and IBM SPSS Statistics for statistical calculations.

The normality of quantitative variables will be assessed using normality tests, such as the Shapiro-Wilk or Kolmogorov-Smirnov tests, as appropriate. To evaluate the homogeneity of variances and sphericity in repeated measures, Mauchly’s test will be applied. To evaluate the efficacy of the intervention, the two groups of the study will be compared: CG and IG at different times (T0, T1, T2, T3). For continuous variables, a repeated measures analysis of variance (repeated measures ANOVA) will be conducted, applied only if the assumptions of residual normality and sphericity are met. In case of violation of the sphericity assumption, Greenhouse-Geisser or Huynh-Feldt corrections will be used to adjust the degrees of freedom. If the variables do not meet the normality assumption or the distribution is clearly non-parametric, the non-parametric Friedman test will be employed to analyze differences between repeated measurements.

The chi-square test will be applied to compare the distribution of qualitive variables between the two groups, such as the presence of comorbidities or the level of motivation to change. To establish statistical significance, a significance level of p < 0.05 will be used.

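### The Bonferroni correction covers all primary and secondary outcomes on the ground that comparisons are few and power is safe; the article's own measures number about 29, and the power claim fails unless effects are very large

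*Protocol article*

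**What the plan says.** The abstract (Design and methodology) names three primaries: "The primary outcomes are sedentary time measured with the Sedentary Behavior Questionnaire (SBQ) and the use of accelerometers, and the state of motivation to change", the last by the transtheoretical-model questionnaire (TMPECQ).

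The Statistical analysis section first sets the nominal level: "To establish statistical significance, a significance level of p < 0.05 will be used". Later, in the paragraph that opens with subgroup analyses, it sets the scope of the correction: "To control for multiplicity across primary and secondary outcomes, the Bonferroni correction will be applied to adjust the significance level and minimize false positives". The next sentence is the justification: "Given the relatively small number of comparisons, this conservative approach is appropriate and unlikely to substantially reduce statistical power".

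The article states no number of comparisons, no adjusted level, and no separate allocation of alpha to the primaries. It also labels no list of secondary outcomes. What is measured appears under Measurements and evaluations.

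**The concern.** The justification is a positive claim about two things, the number of comparisons and the cost in power. Both can be checked against the rest of the article. Many measures are described, and a Bonferroni divisor that includes all of them would make the threshold for sedentary time and motivation very strict. That threshold would also depend on how many routine blood values are counted, which has nothing to do with the question the trial asks.

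At stake is whether the trial can show an effect on its primaries. The sample size offers no margin for this, because it was not derived from power at all. The unstated divisor also matters for conduct. Under Group allocation and masking, the principal investigator collects and analyses the data unmasked, so the size of the family should not be left open until analysis.

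**Working it through.** **1. The plan's own sample size.** Inputs from Sample and recruitment: population 230, 95% confidence, 5% margin of error, 15% dropout. A proportion of 0.5 is assumed, as none is stated.
- n0 = 1.96² × 0.25 / 0.05² = 384.16
- Finite-population correction: 384.16 × 230 / (384.16 + 229) = 144.1
- Dropout: 144.1 / 0.85 = 169.5. The variant n0/(1 + n0/230) gives 143.9 / 0.85 = 169.3.

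This reproduces the stated 169. The formula is one for survey precision and holds no effect size, power or multiplicity term.

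**2. Number of measured outcomes.**

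| Source heading | Measures | Count |
|---|---|---|
| Abstract | SBQ, accelerometer sedentary time, TMPECQ | 3 |
| Anthropometric data | weight, BMI, waist, hip | 4 |
| Clinical characteristics | systolic and diastolic pressure | 2 |
| Clinical characteristics | distinct blood parameters, repeated names counted once | 18 |
| Physical activity level | IPAQ | 1 |
| Quality of life | DQoL | 1 |
| Total | | 29 |

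The 18 blood parameters are glucose, HbA1c and HOMA-IR (3); total, HDL and LDL cholesterol and triglycerides (4); AST, ALT and GGT (3); creatinine, its clearance and urea (3); iron and ferritin (2); sodium and potassium (2); CRP (1).

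Counting blood pressure once and waist-hip once gives 27. The TMPECQ is scored by stage: "The measurement of the questionnaire is performed by analyzing the average score of each corresponding stage of the transtheoretical model of change". Testing five stages instead of one score adds 4 (33); six stages add 5 (34).

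**3. Per-test level.** 0.05/27 = 0.0019; 0.05/29 = 0.0017; 0.05/34 = 0.0015. For comparison, 0.05/3 = 0.0167 and 0.05/10 = 0.005.

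**4. Power.** Assumptions, none of them stated in the article: a two-sided two-sample t-test at one visit, without baseline adjustment, and 72 per arm (84 × 0.85 = 71.4; 85 × 0.85 = 72.25). Power is the probability that a noncentral t with 142 degrees of freedom and noncentrality d × √(72/2) = 6d exceeds the critical value. The critical values are 1.977 at 0.05, 2.423 at 0.05/3, 2.852 at 0.05/10 and 3.195 at 0.05/29. For d = 0.5 the noncentrality is 3.0.

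| Effect (SD) | 0.05 | 0.05/3 | 0.05/10 | 0.05/29 |
|---|---|---|---|---|
| 0.4 | 66% | 49% | 33% | 22% |
| 0.5 | 85% | 72% | 56% | 43% |
| 0.6 | 95% | 88% | 77% | 66% |
| 0.8 | 99.8% | 99% | 97% | 94% |

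The difference detectable with 80% power rises from 0.47 SD at 0.05 to 0.67 SD at 0.05/29.

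**5. The same without choosing an effect.** By the normal approximation, corrected power is Φ(1.96 + z(power at 0.05) − z(1 − 0.05/(2m))). A primary with 80% power at 0.05 has 66% at m = 3, 50% at m = 10 and 37% at m = 29. One with 90% has 80%, 67% and 54%.

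**The case against.** **The count is not the document's.** This stands in part. No secondary list is labelled, and measures such as sodium or ferritin are never called efficacy outcomes. The full protocol may define a shorter family, so 29 is a count of what is measured. However, the general objective covers clinical, biochemical and anthropometric measures as targets, and the conclusion does not need 29: ten comparisons already take 85% to 56% at 0.5 SD.

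**Bonferroni is valid.** This stands. It controls the family-wise error however broad the family, and the article promises confidence intervals. The fault lies in the stated reason and in avoidable loss of power for the primaries.

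**Some loss is unavoidable.** This also stands. With three primaries, Bonferroni costs 85% to 72% at 0.5 SD. The further fall to 43% comes from including the secondaries.

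A reader might infer more than the text supports:
- *That the correction halves power.* This depends on an effect size the article does not give. It is about right for 0.5 SD with 29 tests, but not for 0.6 SD (95% to 66%) or 0.8 SD.
- *That the divisor is the number of outcomes times the number of visits.* The plan analyses continuous outcomes by repeated measures ANOVA over T0 to T3 and specifies no separate test at each visit.
- *That two conflicting thresholds exist.* The 0.05 reads as the nominal level, which the correction then adjusts. A false-positive rate for 29 uncorrected tests would describe testing that is not planned.
- *That a missing rule for discordant SBQ and accelerometer results is an error.* Such detail may sit in the full protocol or analysis plan, which are not shown.

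**Conclusion.** The point holds in this limited form. The correction is written to cover primary and secondary outcomes, the measures in the article number about 29, and the claim that power is unlikely to fall much is wrong except for very large effects. At 0.4 to 0.6 SD, a family of 29 costs 29 to 44 percentage points against 0.05 (95% to 66%, 66% to 22%); at 0.8 SD it costs about 6.

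These figures rest on assumed effect sizes, 72 per arm and a simple single-visit test. The planned repeated measures analysis could give different absolute power, but a threshold of 0.0017 instead of 0.0167 remains a heavy charge on the primaries. Confidence is high that the justification is unsupported, and lower on the exact loss. Type I error is protected. Severity: should be fixed.

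**What to change.** In the Statistical analysis section:

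1. Confine the multiplicity correction to the three primary outcomes, using Holm (never less powerful than Bonferroni) or a prespecified fixed order. If motivation is to be tested by stage, count those tests in the family.
2. Report secondary outcomes as a separate or exploratory family with 95% confidence intervals.
3. Delete the sentence on the number of comparisons and power.
4. Where 0.05 is set, say that it is the family-wise level for the primaries.

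The choice of visit, and any ranking of the two sedentary measures, is for the investigators; this fix does not depend on it.

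The cost is a change of analysis wording, to be made before the data are analysed. The downside is that secondary outcomes then carry no confirmatory claim.

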### Group allocation and masking

The distribution in the CG or IG will be performed sequentially in a 1:1 ratio in order of access to the study, i.e., the first patient who accepts the informed consent will be included in the IG, the next in the CG and so on until the sample is complete. This sequential assignment does not constitute strict randomization, and concealment techniques will not be employed. While this methodology is appropriate for research in real clinical settings, it may carry a risk of selection bias. This risk is acknowledged and will be considered when interpreting the results.

Due to the nature of the intervention, both the participants and the nursing staff and collaborating personnel will be aware of the assigned groups.

Additionally, the principal investigator will be responsible for data collection and analysis; therefore, outcome assessor blinding will not be applied.

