#### Level of sedentary lifestyle.

The level of sedentary lifestyle will be measured with the use of accelerometers and a questionnaire validated in Spanish. The questionnaire used is the Spanish version of the SBQ (S4 Appendix). This instrument measures the time spent in sedentary behaviors from the time the person gets up to the time he/she goes to bed, both during the week and at weekends. The responses are provided on numerical scales, and then the total number of hours spent on each activity is summed. The interclass correlation is 0.83–0.86 and the reliability index of the questions varies from 0.52 to 0.96 [32].

In addition, sedentary time will be evaluated quantitatively using accelerometers. The model used in our study is the ActiTrainer, which is small (8.56 x 3.81 x 1.52 cm) and light (48 g), ensuring great comfort during use. Previous studies have supported its use for an objective and more reliable measurement of the effectiveness of interventions [33–38] They will be placed by the study nurse during the measurement periods (T0-3), however, both the participants of the CG and the IG will receive training on their proper placement, removal and protocol. These should be worn at the waist, fastened with a well-fitting elastic belt, placed in the morning and removed at bedtime and during periods of exposure to water (bath, shower, swimming, etc.). To avoid skin irritation in case of incorrect fit, they may be worn over clothing. Participants must wear the device for 5 consecutive days, with a minimum of 10 waking hours per day.

This device only detects human movement, electronically filtering high-frequency vibrations produced by cars, buses, trains, etc. It has no other function than to measure physical activity through an encryption of internal operations that require specific software and cannot be used for any other purpose. It does not emit radiation or interfere with the human body. However, any eventuality must be reported.

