It is important to note that education should not be understood as a one-time action, but as a continuous process that requires follow-up and personalized attention [50]. And to achieve successful management of patients with chronic diseases, such as diabetes, the focus should be on self-management, allowing patients to take an active role in their health care [51,52]. In this sense, our intervention combines face-to-face methods, both group and individual, with non-face-to-face strategies through telephone calls, as it constitutes a key strategy for personalized management. This modality makes it possible to address the specific problems and concerns of each patient during the process, generating a positive impact on their physical and psychological well-being, in addition to facilitating access to a greater number of people, regardless of socioeconomic level [53]. However, it is important to emphasize that, despite the benefits of non-face-to-face interventions, these should not be the only form of care. The lack of face-to-face interaction can make it difficult to build a trusting relationship between patient and health professional, which could decrease patient satisfaction and engagement with their treatment [54,55]. In addition, the use of digital technologies can generate insecurity in some patients, increasing levels of anxiety or depression, especially in those with little experience in handling new technological tools [56,57]. Therefore, it is crucial to complement remote interventions with face-to-face interventions, which allow a more comprehensive physical and emotional assessment, and strengthen the bond between nurse and patient [58].

The study’s interventions have a personalized approach, which considers individual preferences and needs to consolidate the new habits acquired in the long term. Another strength of the study lies in the measurement of the main objective, as it is carried out using questionnaires and accelerometers, allowing a more objective and accurate measurement of the results. The study design, moreover, is oriented to be applicable in the health system, promoting a more efficient use of available resources. And the 12-month intervention, with an intensive focus in the first 6 months, can be easily managed by nurses. Furthermore, the study has a design that offers the possibility of generating solid, high-quality evidence on the benefits of the proposed intervention.

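### Self-reported (SBQ) and device-measured sedentary time are both primary with no rule on which decides, and both are called objective in an unblinded trial that coaches only one arm

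*Protocol article*

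**What the plan says.** The abstract (Design and methodology) states: "The primary outcomes are sedentary time measured with the Sedentary Behavior Questionnaire (SBQ) and the use of accelerometers, and the state of motivation to change". The last of these is measured by the motivation questionnaire (TMPECQ). No order is given among the measures, and no rule for the case in which the two sedentary-time measures disagree.

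Under Level of sedentary lifestyle, the SBQ is a questionnaire on the participant's waking-day sedentary activities: "The responses are provided on numerical scales, and then the total number of hours spent on each activity is summed". The same section presents the accelerometer as the objective and more reliable way to judge an intervention.

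The Statistical analysis section treats the two alike. It says "The reliability and validity of the instruments used, such as the SBQ and the ActiTrainer accelerometer, have been verified", and the next sentence is "These instruments will measure sedentary lifestyle in an objective and reliable manner". The Discussion counts as a strength that measurement of the main objective "it is carried out using questionnaires and accelerometers, allowing a more objective and accurate measurement of the results".

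On masking (Group allocation and masking), "both the participants and the nursing staff and collaborating personnel will be aware of the assigned groups", and "the principal investigator will be responsible for data collection and analysis; therefore, outcome assessor blinding will not be applied".

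Under Study activities, the IG has group sessions on the risks of sedentary habits, motivational calls in which progress in cutting sedentary time is evaluated, and a nurse visit that reviews the same progress. The control group (CG) receives two-monthly e-mails on healthy habits and standard educational material.

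**The concern.** The SBQ asks about the behaviour that nurses coach and review in one arm only. IG participants may therefore report fewer hours without sitting less. That bias differs between arms, so it goes straight into the group comparison, and neither a larger sample nor a stricter significance level corrects it.

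A self-reported primary outcome in an unblinded behavioural trial is common and can be defended if the plan says how far it is trusted. Here the plan does two things that work against that. It describes the questionnaire as objective, and it ranks the questionnaire level with a device measure that does not depend on recalled hours. If the SBQ shows a difference and the accelerometer does not, nothing in the protocol stops the SBQ result from being reported as the primary effect. The person who would make that choice collects and analyses the data unblinded.

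**Working it through.** **1. Is the description of the SBQ consistent?** The Level of sedentary lifestyle section describes reported hours that are summed, and ties objectivity to the accelerometer. The figures it gives for the SBQ (correlation 0.83–0.86, item reliability 0.52–0.96) concern reliability. They do not address bias when respondents know their arm. The Statistical analysis section then applies the word objective to both instruments. The two sections do not agree.

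**2. Is precedence set anywhere?** The Statistical analysis section uses accelerometer sedentary time for the correlations with clinical parameters. For the comparison of CG with IG it names no deciding measure.

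**3. The plan's own sample size.** Inputs from Sample and recruitment: N = 230, 95% confidence (z = 1.96), margin e = 0.05, dropout 15%. Assumed: p = 0.5.

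n = N·z²·p(1−p) / [e²(N−1) + z²·p(1−p)] = 230 × 0.9604 / (0.5725 + 0.9604) = 144.1

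144.1 / 0.85 = 169.5, which agrees with the stated 169. This is a survey-precision calculation. It contains no SBQ mean, SD or target effect, so it gives no scale for a reporting bias.

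**4. What a reporting shift could do.** Assumptions: no true effect; a shift of b SD in the IG only; a two-sided comparison of two means at one visit; 72 per arm (84 × 0.85 = 71.4 and 85 × 0.85 = 72.25).

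Noncentrality = b × √(72/2) = 6b. The chance of a significant result favouring the IG is Φ(6b − z), where z is the two-sided critical value: 1.960 at 0.05, 2.394 at 0.05/3 and 3.023 at 0.05/20.

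| Shift b (SD) | 6b | α = 0.05 | α = 0.05/3 | α = 0.05/20 |
|---|---|---|---|---|
| 0.2 | 1.2 | 22.4% | 11.6% | about 3% |
| 0.3 | 1.8 | 43.6% | 27.6% | about 11% |
| 0.5 | 3.0 | 85.1% | 72.8% | about 49% |

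With no bias the chance at 0.05 is 2.5%. The 0.05/3 column corrects for the three primary measures only. The plan applies Bonferroni across primary and secondary outcomes but gives no count. Twenty is an assumption, prompted by the 18 or so blood measures listed under Clinical characteristics.

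**5. Sensitivity.** The shift that gives a 50% chance is z × √(2/n). For 72 per arm it is 0.33 SD at 0.05 and 0.40 SD at 0.05/3. For 84 per arm (everyone assigned) it is 0.30 and 0.37 SD.

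**The case against.** **Multiplicity.** The 0.05 column is not the plan's own test, because Bonferroni is specified. This stands: the 22%, 44% and 85% must not be quoted alone. But Bonferroni only raises the shift needed for significance. It does not remove the bias.

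**Size of the bias.** A reader might take the ten-hour daily average cited in the Introduction, assume 5–10% under-reporting, and infer a spurious 30–60 minutes a day. The protocol gives no SBQ SD, so those minutes cannot be converted to SD units, and the under-reporting rate is itself a guess. The planned analysis is also repeated measures ANOVA with multiple imputation, not a single-visit test. These points stand, and the table is illustrative only.

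**Contrast between arms.** A reader might infer that controls have no idea which answer is wanted. The documents do not support that: CG e-mails stress an active lifestyle, and the project is explained to everyone at consent. What is confined to the IG is the coaching and the nurse review of progress.

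**Decision rule.** A reader might infer that success on either measure is enough. The protocol does not say so. If both had to succeed, SBQ bias alone could not produce a positive finding on sedentary time. It does not say that either, and the gap is the point.

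**Candour.** A reader might infer that the lack of blinding is passed over. It is not: the Discussion admits that it may affect objectivity. It does so in general terms, without linking it to the SBQ or giving the device precedence. The Discussion sentence on strengths is comparative and does not call the SBQ alone objective.

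**Limits of the remedy.** The TMPECQ is also a primary, unblinded self-report and remains so. Participants also know when they wear the accelerometer and may behave differently on those days. Both points are true. They limit what the fix achieves without removing the reason for it.

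**Conclusion.** The point holds in this form: two primary measures of sedentary time have no stated precedence, one of them is unblinded self-report, and the Statistical analysis section describes it as objective. A significant SBQ difference could therefore be reported as a primary effect when it reflects differential reporting.

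How likely that is cannot be known from the protocol. Under the stated assumptions, shifts of 0.2 to 0.5 SD give from about 3% to 85%, depending on the shift and on how many comparisons Bonferroni covers. The documents do not show that such a shift will occur, or that a positive result would be spurious. Both data streams are collected in any case, so a disagreement would be visible. This should be fixed, and before results are seen, but it does not invalidate the design.

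**What to change.** - Name accelerometer sedentary time as the deciding primary measure of sedentary behaviour and make the SBQ supportive. State that no claim of reduced sedentary time will rest on the SBQ alone.
- In the Statistical analysis section, apply the word objective to the ActiTrainer only and describe the SBQ as unblinded self-report.
- Note that the TMPECQ is also unblinded self-report, and that a TMPECQ result alone will not be presented as evidence of reduced sedentary time.

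**Cost.** No new data: the accelerometer is already worn in both arms at T0 to T3, with validity rules set out. The change is more than wording, because altering the rank of a primary outcome needs a registry update and, under Ethical approval, a substantial modification must be approved by the committee before it is implemented. Participants without a valid accelerometer record would be imputed for the deciding measure under the planned multiple imputation.
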